#### Primary outcome measure

##### Assessment of DSM-IV Personality Disorders (ADP-IV)

The ADP-IV is a Dutch self-report questionnaire intended for the assessment of PD characteristics [54]. This measure consists of 94 items, with two questions each. First, on a 7-point Likert scale, the participant indicates the presence of a trait (i.e. the trait score). Then, if the trait is present, i.e. rated as five or higher, the participant specifies the associated degree of distress on a 3-point Likert scale (i.e. the distress score). The ADP-IV allows for a categorical diagnosis. A trait is rated as present when the trait score is rated higher than four and the distress score higher than one. The ADP-IV also allows for a dimensional total score by summing all trait scores. The total score has demonstrated good internal consistency (*α* = .85) and the subscales for the specific PDs range from questionable for schizoid PD (*α* = .6) to good for avoidant PD (*α* = .84), with a median acceptable internal consistency (*α* = .77 [54]). Validated translations are available as well.

##### Clinician-Administered PTSD Scale for DSM-5 (CAPS-5)

The CAPS-5 is a structured diagnostic interview used for measuring the severity of PTSD [11]. The CAPS-5 provides severity ratings for twenty DSM-5 PTSD symptoms on a scale of 0 to 5. Summing these severity scores results in a total PTSD severity score. Ten other questions regard the duration of the symptoms, impairment resulting from the symptoms, and dissociative symptoms. The assessors in the current study will be or have already been trained in the administration of the CAPS-5. Psychometric evaluation demonstrates a high internal consistency (*α* = .9) and interrater reliability (ICC = .98 [12]).

#### Secondary outcome measures

##### Structured Clinical Interview for DSM-5 Personality Disorders (SCID-5-P)

The SCID-5-P is a structured diagnostic interview used for the evaluation of DSM-5 PDs [28]. It provides severity ratings of each PD symptom on a 3-point scale. Based on these ratings, a symptom can be assessed as present or absent [2]. In total, 135 questions inquire into the presence, examples and explanations of a symptom. Sometimes, multiple questions refer to the same symptom to capture the diverse aspects of the criterium. The SCID-5-P should exclusively be administered by trained clinicians as it requires clinical interviewing skills and the ability to add questions. The assessors in the current study will be or have already been trained in the administration of the SCID-5-P. Reliability and validity data of the Dutch SCID-5-P are not yet available, but they are expected to equal the nearly identical previous version, the Structured Clinical Interview for DSM-IV Axis II Personality Disorders (SCID-II [68]). Interrater agreement on the relevant scales of the SCID-II appears substantial to almost perfect (*κ* = .78-.98 [46, 47]).

##### Treatment Inventory of Costs in Patients with psychiatric disorders (TiC-P)

The TiC-P is a Dutch self-report questionnaire used for the evaluation of costs related to psychosocial problems, such as a psychologist or medication (http://www.imta.nl/questionnaires/). The TiC-P is divided into three parts. The first part consists of fifteen questions pertaining whether and to which degree the respondent has used certain mental health care utilities in the last 3 months. The second part consists of a shortened version of the Health and Labour Questionnaire. Eleven questions record the degree to which psychosocial problems have hindered the respondent in (paid and unpaid) work. A third part consists of some general questions about the respondent. To reach a total cost score, the frequency of healthcare consumption/productivity loss is multiplied by a monetary value. Test-retest analyses have shown that the TiC-P is reliable, with agreement of the first part ranging from moderate to almost perfect (*κ* = .49–.84) and agreement of the second part being substantial (*κ* = .65–.76 [13];).

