## Method

### Design

The TEMPO study is a single-blind randomized controlled superiority trial with two arms, i.e. EMDR therapy and waiting list. The trajectory of a participant through the study is shown in Fig. 1. The experimental group will receive ten bi-weekly EMDR sessions of 90 min each, with a total duration of 15 h of treatment over 5 weeks. The groups are compared at baseline (pre-randomization; T0), post-intervention (after 5 weeks; T1), 3-month (T3), 6-month (T6) and 12-month (T12) follow-up. At baseline, demographical data will be collected for predictive analyses of treatment success and treatment dropout. At T1, patient dropout will be recorded and a random selection of patients in the experimental condition will be interviewed to assess their experiences with EMDR therapy. Until T3, patients do not receive further treatment, except in a crisis situation. At T3, all patients will be invited by their therapist for a consultation to examine whether (further) treatment is necessary. Any available treatment, except EMDR therapy, will be offered. At T12, when participation is concluded, control patients will also be offered the opportunity to receive EMDR therapy.

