### Measurements

There will be five measurement moments, namely at baseline (T0), post-intervention (T1), 3-month follow-up (T3), 6-month follow-up (T6) and 1-year follow-up (T12). While most measures will be conducted at each measurement moment (see Table 1), the Childhood Trauma Questionnaire and the Life Events Checklist will only be administered at baseline and the interview about patients’ experiences with EMDR therapy is exclusively conducted at T1, with only the experimental group. All measurements will take place at the location at which the participant is in treatment or through video calls. The self-report questionnaires will be digitally administered with Data Manager, which automatically invites participants through email on pre-determined dates and then stores the responses safely. Participants will be reminded to fill in the questionnaires, first by mail and second by telephone, to promote complete follow-up data. At baseline, demographical data are collected. Results will be recorded as absolute values.

**Table 1 Tab1:** Schedule of enrolment, interventions and assessments

Timepoint	Study period							
				Post-allocation				
	Enrolment	T0	Allocation	Intervention	T1	T3	T6	T12

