This study has a number of strengths. Firstly, it is a multicentre, outpatient trial that includes a wide variety of PD patients and EMDR therapists, enhancing the external validity of the study. Secondly, a broad range of outcome measures is used in addition to measures of PD symptomatology, such as measures involving cost-effectiveness, and severity of trauma symptoms, which is likely to extend the literature on the effectiveness of EMDR therapy for (sub-threshold) PTSD in comorbid PTSD and PD populations, functioning, quality of life and patients’ experiences with EMDR therapy. Thirdly, the study includes multiple follow-up measurements, documenting the longevity of the hypothesized effects. Fourthly, treatment protocol adherence by EMDR therapists will be evaluated utilising a stopwatch and video recordings. These types of measures can help therapists to stay focused, not to elaborate, and to encourage sticking to the protocol. In addition, it will be possible not only to count the number of sessions, but also to calculate the average therapy time, and of course to determine afterwards to what extent the protocol was applied correctly. Also, some weaknesses of the study should be noted that cannot be avoided for ethical reasons. Firstly, blinding participants in the experimental condition is impossible and participants in the control condition should be informed of their allocation. Expectancy-effects might therefore influence the results. However, at all times, assessing researchers are blinded to the condition the participant is in. Secondly, after three months of follow-up, patients will be offered further treatment. The type of treatment, and therefore the intensity and duration of the treatments, may vary substantially among participants. However, the measurements used for the cost-effectiveness analyses include measures of healthcare consumption, allowing collection of exact data on the interventions that patients receive after T3. With these data, differences in health care utility between the control and experimental group can be explored.

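### Three months of health care use between T6 and T12 fall outside every TiC-P recall window, so the claim of exact data on care after T3 does not hold

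*Protocol article*

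**What the plan says.** The TiC-P section describes a three-part self-report questionnaire. Part 1 asks "whether and to which degree the respondent has used certain mental health care utilities in the last 3 months". Part 2 concerns productivity: "Eleven questions record the degree to which psychosocial problems have hindered the respondent in (paid and unpaid) work". No recall period is given for part 2. Costs are then built as follows: "To reach a total cost score, the frequency of healthcare consumption/productivity loss is multiplied by a monetary value".

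The Design section gives the timing. T0 is before randomisation, and the later visits are "post-intervention (after 5 weeks; T1), 3-month (T3), 6-month (T6) and 12-month (T12) follow-up". Table 1 marks the TiC-P at T0, T1, T3, T6 and T12, with nothing between T6 and T12.

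The EMDR therapy and Waiting list sections both hold back treatment for the personality disorder until T3 has passed. The Analyses section names the TiC-P as the source for medical service use and productivity loss, and names no other.

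The Discussion concedes that treatment after T3 may vary widely between patients. It answers that the cost measures record health care consumption, "allowing collection of exact data on the interventions that patients receive after T3".

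**The concern.** The recall period and the visit spacing do not match at the end of follow-up. A 3-month look-back at T12 cannot reach T6, so a block of care use is never asked about.

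The position of the block is what makes it matter. Cost-effectiveness is a declared aim, and the Discussion hypothesises that EMDR will shorten later treatment and lower its cost. That later treatment begins only after T3, so the gap lies in the middle of the period in which the hypothesised saving would appear. If the arms differ in care use during those months, the incremental cost, the cost per QALY and the acceptability curve can all be wrong, in either direction.

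The opposite mismatch occurs at T1. Its 3-month look-back is longer than the 5 weeks since baseline, so it reaches into time before randomisation.

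**Working it through.** **Inputs.** Recall for care use: 3 months (TiC-P section). T1 at 5 weeks, then 3, 6 and 12 months (Design). TiC-P at T0, T1, T3, T6 and T12 (Table 1). Usual care after T3 (EMDR therapy; Waiting list). Conversion: 1 month = 52.18/12 = 4.348 weeks, so 3 months = 13.0 weeks.

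**The plan's own interval.** The Design section gives "ten bi-weekly EMDR sessions of 90 min each, with a total duration of 15 h of treatment over 5 weeks". At two sessions a week, 10/2 = 5 weeks, and 10 × 1.5 h = 15 h. The 5-week T0-T1 interval is reproduced.

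**Visit clock.** The Waiting list section places T3 three months after T1, which points to clock A (months counted from T1). Clock B (months counted from T0) is run as well.

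**Coverage.** Each window runs from (visit − 13.0 weeks) to the visit, in weeks from T0:

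| Visit | Clock A window | Clock B window |
|---|---|---|
| T1 | −8.0 to 5.0 | −8.0 to 5.0 |
| T3 | 5.0 to 18.0 | 0.0 to 13.0 |
| T6 | 18.0 to 31.1 | 13.0 to 26.1 |
| T12 | 44.1 to 57.2 | 39.1 to 52.2 |
| Not covered | 31.1 to 44.1 | 26.1 to 39.1 |

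**Size of the gap.** Spacing minus recall = 6 − 3 = 3 months (13.0 weeks) on either clock.
- Share of the T3-T12 period: 3/(12 − 3) = 33% on either clock.
- Share of the time from randomisation to T12: 13.0/57.2 = 23% (A) or 13.0/52.2 = 25% (B).

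**T1 window.** 13.0 − 5 = 8.0 weeks lie before T0, and 8/13 is about 62% of the window. These weeks were already asked about at T0. On clock B the T3 window also covers the 5 weeks from T0 to T1 a second time. On clock A the T1, T3 and T6 windows adjoin without overlap.

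**Illustration of what the gap can hide.** The Introduction reports mean treatment durations of 168 to 504 days, average 358, in reviewed trials. Assume a course starts at T3.
- The shortest mean course, 168/30.4 = 5.5 months, ends at about month 3 + 5.5 = 8.5. Then 8.5 − 6 = 2.5 of its 5.5 months (about 46%) fall in the gap.
- A course of average length, 358/30.4 = 11.8 months, runs through the whole gap.

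A patient in care at T6 who reports none in the T12 window could have stopped at any time in between.

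**Check of the remedy.** With a 6-month recall at T12, or an added questionnaire 3 months after T6, uncovered time falls from 13.0 to 0 weeks. With a T1 recall limited to time since baseline, the part before randomisation falls from 8.0 to 0 weeks.

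**The case against.** The strongest reply is that the article does not say how the window costs become a 12-month total. Interpolation between T6 and T12, or trimming of T1, could sit in an analysis plan that is not shown, and the full protocol might adapt the recall at T12. It can also be said that this is a secondary economic evaluation, that the primary outcomes are untouched, and that much later care may be on file at the two institutions.

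Much of this stands as a limit on size. It does not remove the point. The article states a 3-month recall without qualification, shows no extra administration, and claims exactness for the very period that contains the gap. Interpolated months are assumed, not observed, and the assumption concerns when care stops, which is what the economic hypothesis is about. If the trial does use an adapted recall, the TiC-P section misdescribes it. If not, the Discussion is wrong. One of the two texts needs correcting.

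Four stronger readings are tempting, and the documents do not support them.
- A reader might infer that costs from before randomisation bias the incremental cost through T1. T0 precedes randomisation, so those 8 weeks should be similar in both arms on average. They raise cost levels and add noise. Nor does any section say that the T1 answers will be summed untrimmed.
- A reader might extend the gap to productivity costs. The recall for part 2 is not stated, so the gap is shown for care use only.
- A reader might quote a flat 25% of follow-up. That holds only if months are counted from T0; counted from T1 it is 23%.
- A reader might conclude that incremental costs are shown to be biased. Only unobserved time is shown. Bias also needs a difference between the arms in the gap that the neighbouring windows do not reflect, and neither its direction nor its size can be derived from the document.

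**Conclusion.** The point holds for health care use between T6 and T12. As the article is written, 3 of the 9 months after T3 (33%), or 23-25% of the time from randomisation to T12, are covered by no questionnaire. The claim of exact data on care after T3 therefore does not hold. Incremental costs may be biased in either direction if usual care differs between arms in those months; the amount is unknown.

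This rests on three things: the 3-month recall applies at T12 as stated, Table 1 lists every TiC-P administration, and no second source of resource use exists. It does not depend on the visit clock.

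The T1 overlap of about 8 weeks is a minor matter of window handling. It would shrink if T1 fell later than 5 weeks, and would vanish at about 13 weeks.

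**What to change.** **At T12,** ask about care use since the last assessment (6 months), or send one extra online TiC-P midway between T6 and T12. The Measurements section already describes automatic e-mail invitations on set dates, so either change is small. The longer recall brings more recall error. The extra questionnaire brings slight patient burden and, if paid like a full measurement (an assumption), at most 159 × 25 = 3,975 euros.

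**For patients already past T12,** use the two institutions' treatment records for the missing months. This is a partial source, since care received elsewhere would not appear in it. Report the gap as a limitation.

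**At T1,** limit the recall to the time since baseline, or trim those answers to the 5 weeks after T0 in the analysis. If follow-up is counted from T0, limit T3 to the time since T1 as well, to avoid counting 5 weeks twice.

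**In the text,** correct the Discussion's statement on exact data, and state the recall period for the productivity part so that its coverage can be checked in the same way.

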##### EuroQol—5 dimensions—3 levels (EQ-5D-3L)

The EQ-5D-3L [27] is a self-report questionnaire that measures generic health. It consists of two parts. The first part assesses health in five dimensions (mobility, self-care), each of which has three levels of responses (no, some or extreme problems). Results can be reported as a health state. For example, someone with health state 11223 experiences no problems in the first and second, moderate problems in the third and fourth and severe problems in the fifth dimension. Health states can then be assigned an index score based on societal preference weights for the health state [43, 65]. The second part consists of a visual analogue scale ranging from zero to hundred or from worst to best imaginable health. Respondents are asked to indicate their health condition. A Dutch translation will be used.

##### Mental Health Quality of life (MHQoL) questionnaire

The MHQoL is a self-report quality of life measure, recently developed for use in people with mental health problems (https://www.imta.nl/mhqol/). It consists of eight items. The first seven items refer to specific aspects of mental health (e.g. independence, relationships). Respondents are asked to rate their degree of satisfaction within these mental health aspects on a four-point Likert scale. By summing the responses on these seven items, an index score is calculated. The eighth item inquiries about general psychical wellbeing with a visual analogue scale, ranging from zero to ten or worst to best imaginable psychical wellbeing. Internal consistency is high for the total score of the Dutch version (*α* = .85 [63]).

##### Life Events Checklist for the DSM-5 (LEC-5)

The LEC-5 is a self-report questionnaire that evaluates potential experiences with a wide array of traumatic events [31]. It consists of seventeen items, each a potentially traumatic event (e.g. assault with weapon). Additionally, it uniquely inquires about various types of exposure to each potentially traumatic event. Concretely, respondents rate their experiences with each event on a five-point Likert scale: 1 = happened to me; 2 = witnessed it; 3 learned about it; 4 = not sure; and 5 = does not apply. Thus, it captures elements that may be overlooked by other measures; learning about a natural disaster, for example, might be quite traumatic. A Dutch version will be used, which has not yet been evaluated. However, agreement for the original scale is substantial (*κ* = .61 [31]).

##### PTSD Checklist for DSM-5 (PCL-5)

The PCL-5 is a self-report questionnaire used for assessing PTSD [66]. On a five-point Likert scale, respondents are asked to indicate to which degree they suffered from twenty PTSD-related problems (e.g. reoccurring unpleasant dreams) in the last month. The problems are divided into four subscales: (1) intrusive recollections, (2) avoidance/numbing, (3) cognition/mood and (4) arousal but can be summed to yield a continuous measure of PTSD symptom severity [10]. A Dutch translation will be used, of which the total score has excellent internal consistency (*α* = .93 [64]).

##### Childhood Trauma Questionnaire—Short Form (CTQ-SF)

The CTQ-SF is a self-report questionnaire intended as a screening measure for maltreatment histories in both clinical and non-referred groups [8]. On five-point Likert scales, respondents are asked to indicate the degree of truth of 25 statements about childhood trauma (e.g. ‘I was molested’ or ‘I had to wear dirty clothes’). The CTQ-SF consists of five subscales: physical and emotional neglect and physical, emotional and sexual abuse. A Dutch translation will be used, of which the scales have good to excellent internal consistency (*α* = .89–.95), except for the physical neglect scale, which has questionable internal consistency (*α* = .63 [62]).

##### Difficulties in Emotion Regulation Scale (DERS)

The DERS is a self-report questionnaire, developed for the measurement of clinically relevant difficulties in emotion regulation [30]. On a five-point Likert scale, the respondent indicates the frequency of 36 emotion regulation-statements (e.g. ‘I know how I feel’, ‘when I am upset, I lose control over my behaviour’). The DERS consists of six subscales, namely: lack of emotional clarity, lack of emotional awareness, impulsivity, non-acceptance of emotional responses, limited access to emotion regulation strategies and difficulties engaging in goal-directed behaviour. Whereas the English DERS has demonstrated excellent internal consistency in a BPD sample (*a* = .94 [30]), the subscales of the Dutch version have shown good internal consistencies in an adolescent sample (average *a* = .81 [52]).

##### Brief State Paranoia Checklist (BSPC)

The BSPC is a self-report questionnaire that measures paranoid thinking [53]. On a ten-point Likert scale, the respondent is asked to indicate the current applicability of five statements regarding paranoid ideation, where a higher score indicates greater paranoid thinking. The scale has demonstrated good internal consistency (*α* = .83 [53]).

##### Level of Personality Functioning Scale—Brief Form 2.0 (LPFS-BF 2.0; LFPS)

The LPFS is a self-report questionnaire intended for assessing personality functioning based on the alternative DSM-5 models for PDs [1, 35]. Specifically, it measures interpersonal and self-functioning, as are its two subscales. On a four-point Likert scale, the respondent is asked to indicate the applicability of twelve statements referring to interpersonal or self-functioning. The internal consistency estimates of the Dutch version are high for the total scale (*α* = .82), the self- (*α* = .79) and interpersonal (*α* = .71) functioning scales [67].

##### Outcome Questionnaire (OQ-45)

The OQ-45 is a self-report questionnaire, devised for repeating measurements of client status through the course and at termination of therapy [42]. With 45 broad-ranging health-related statements, where the respondent indicates their applicability on a five-point Likert scale, it measures three domains of functioning; symptom distress, interpersonal relations and social role. A Dutch translation will be used. In clinical samples, it has demonstrated excellent internal consistency for the total score (*α* = .93), but questionable internal consistency for the social role subscale (*α* = .69) [20].

##### Interview

To evaluate patients’ experiences with EMDR therapy, an interview was designed (see Appendix A and B). A non-blind researcher checks every fifth participant (e.g. 5, 10, 15…) to determine whether this person is in the EMDR treatment condition. If so, the person will be invited for the interview after T1. If not, the researcher will check the next participant (e.g. if participant 15 is in the control condition, the researcher checks participant 16), until an EMDR participant is found. Interested participants will be interviewed by the researcher. In qualitative research, sample sizes are difficult to predict. Namely, in general, inclusion is continued until the interviews provide no further information. Yet, as an estimate, about twenty interviews will be sufficient to answer the research question. The interview consists of 13 open questions, which start generic, but gradually become more and more specific, so that most aspects of their experiences with EMDR therapy are covered.

